## 1 CONTEXT AND JUSTIFICATION

### 1.1 Context

This protocol has been written in a context of extreme urgency. The epidemic, which is destabilising the care system of numerous countries and several regions of France, is growing in power in the Nouvelle-Aquitaine region. In a few days, it is possible that the care systems will be overwhelmed in some areas of the country. In this context, home-based treatment of people affected by COVID-19 will become a major part of the response, to provide relief for emergency and hospital services, by avoiding clinical deterioration in people who are most at risk of developing a severe form of the disease, requiring hospitalisation. There is therefore a twin threat to individual and public health level.

The urgent implementation of a home-based screening and follow-up model, allowing clinical monitoring according to the regulatory and ethical requirements of clinical research, raises enormous logistical challenges. The solutions adopted should be adjusted to circumstances, including shortages of Personal Protective Equipment or tests and clogging of the emergency services, screening centres or laboratories. This adjustment will perhaps require rapid organisational decisions in the days before the start of the trial, perhaps even during it. This is the reason why the text of this protocol refers back to the procedures for certain roll-out details, with the note “[SDPM]” {See Details in Standard Operating Procedures}”. The drafting and evolution of such procedures shall be monitored in particular: (i) by the Scientific Advisory Board (SAB) and by the independent data and safety monitoring board (DSMB), which meet on a frequent basis, (ii) by the Institutional Review Board (IRB), to authorise implementation.

### 1.2 Justification

For adults aged 65 years or more affected by the disease COVID-19 at an early phase and without hospitalisation criteria, early treatment could prevent hospitalisation or death. No treatment has currently been validated in this indication (1). The majority of clinical trials for COVID-19 in progress or planned are hospital-centered and enrol patients at a later stage of the disease (2). Optimising treatment at home could reduce the workload in hospitals and improve individual results. This is one of the greatest challenges to be overcome in the weeks to come.

Among risk factors of clinical deterioration in patients with COVID-19, age is described as the most important (3–6). Admission of elderly people suffering from the disease in Intensive Care Units is sometimes limited, justifying the major interest in avoiding the severe forms, which are not necessarily treated in the best way, in the context of an epidemic (7,8).

We are proposing a trial to evaluate the tolerance and efficacy of potential drugs for this indication, while considering the following points:

- Preclinical arguments suggesting an antiviral activity against SARS-CoV-2 already exist for several drugs. Numerous pre-clinical and clinical research projects are in progress on this topic. Ongoing clinical trials must be able to adapt and rapidly change their therapeutic strategies, when new evidence emerges.
- Rapid implementation of a clinical trial for people confined at home poses numerous challenges. Feasibility should be checked, without delaying the evaluation of efficacy.

These points imply the need for a trial comparing the absence of a specific curative treatment (current situation) with experimental curative treatments: (i) starting with available drug candidates, yet allowing consideration of new candidates at any stage; (ii) allowing the interruption of inefficacious treatments (on the basis of futility criteria) or toxic ones.

In response to this situation, we have designed the project as a multi arms and multi stages (MAMS) randomised controlled trial. The trial is to start in Bordeaux and the surrounding area. It could be extended to several European or African partner countries. Discussions have already begun on this with Spain, Italy, Ivory Coast, Senegal and Burkina Faso. In the event of being extended, each country will have its own protocol, yet with a common design, allowing common analyses. The current version of the protocol describes the study, which is being rolled out in Bordeaux and the surrounding area.

### 1.3 Data on the effectiveness of drugs against SARS-CoV-2

There are available data on the effectiveness of several drugs against SARS-CoV-2 and other coronaviruses. They mainly come from *in vitro* studies and rarely from animal and human studies. Currently, there is no data from randomised trials showing the clinical benefits of using one of these drugs. Many are in progress or planned, but of the 115 ongoing

therapeutic trials targeting SARS-CoV-2 infection registered up to March 7th 2020 on [clinicaltrials.gov](https://clinicaltrials.gov), WHO and the Chinese registers of clinical trials, we have found no trial specifically targeting ambulatory patients presenting at increased risk of hospitalization or death (2).

### 1.3.1 Protease inhibitors

Lopinavir/ritonavir (LPV/r) is a fixed-dose combination used to treat HIV infection. It has shown to be effective *in vitro* against SARS-CoV-2 in several studies and seems to be effective against MERS-CoV in animal studies (9). Lopinavir and ritonavir link up *in vitro* at the active site of the SARS-CoV protease (10) and initial virtual anchoring studies have confirmed that the spatial structure of the linkage site of LPV/r is conserved between SARS-CoV and the SARS-CoV-2 (11). Within a cohort of 111 patients infected with SARS-CoV, use of LPV/r has been associated with better clinical results (12). Use of this agent in treating COVID-19 has been described in case series of patients infected with SARS-CoV-2 in Singapore, with variable clinical results (13–20). This data has led to the registration of more than 15 clinical trials of LPV/r for COVID-19 in the clinical trials register of USA and China. WHO shortlisted LPV/r as a promising candidate for the treatment of COVID-19 (16). LPV/r has been included as a recommended treatment for COVID-19 in some national guidelines, including in China and France (17,18). Even if a randomised trial held in China has not demonstrated the superiority of LPV/r as compared to standard of care (19), this drug should continue to be evaluated. The problem is that ritonavir interacts with numerous drugs, which might be taken by elderly people and quite frequently causes secondary digestive effects, especially diarrhoea, which could, in association with COVID-19, lead to severe dehydration (20). We have therefore not retained this option.

We intended to replace it with another protease inhibitor, darunavir/cobicistat, suggested as a potential candidate for treating COVID-19 (21). A molecular modelling study suggests that darunavir/cobicistat could attach itself to the papain domain of SARS-CoV-2 viral protease, bringing about small changes in the conformation of the protease (22). Use of darunavir/cobicistat for COVID-19 has been reported in a pre-publication by Chinese authors (23). Four clinical trials are being prepared. It is also mentioned as a second line option in the treatment of COVID-19 patients in Chinese recommendations (24). Johnson & Johnson, however, has recently highlighted the absence of supportive evidence for the use of darunavir/cobicistat at this stage (25). Even though better tolerated than LPV/r, nevertheless, we have no longer retained this trial, for fear of risking potential drug-drug interactions with ritonavir or cobicistat among elderly.

### 1.3.2 Chloroquine and hydroxychloroquine

Even if the efficacy of chloroquine on a certain number of viruses has been described *in vitro* (26,27), it has not demonstrated any clinical benefit in treating influenza, dengue or chikungunya (28–30). Since the start of the COVID-19 pandemic, several publications have reported some efficacy of chloroquine against COVID-19 and mentioned clinical efficacy (31–37). However, published studies to date are either non-comparative or of an insufficient sample size. Chloroquine having previous usage, being easy to administer and well tolerated, it is logical, in the absence of any conclusive result, to evaluate it in an outpatient treatment trial. The mechanism action of chloroquine and hydroxychloroquine being similar (36) and the pharmacokinetic data showing that hydroxychloroquine was more powerful on cells infected with SARS-CoV-2 than the chloroquine phosphate (37) it is also logical to use hydroxychloroquine rather than chloroquine in such trials, especially as pharmacokinetic models predict that hydroxychloroquine could have a better diffusion in pulmonary fluids (37) and as it is better tolerated.

In the light of such data, on March 7th 2020, 18 clinical trials evaluating hydroxychloroquine or chloroquine have been registered on [clinicaltrials.gov](https://clinicaltrials.gov). The dose for COVID-19 to be evaluated has been a matter of debate. In a recent, single-arm trial in France, the daily hydroxychloroquine dose was 600mg. Chinese guidelines on COVID-19 currently recommend a dose of 400mg twice a day for 2 days, followed by 200mg twice a day over 4 days. Italian guidelines also use a loading dose of 400mg per day over 2 days, followed by a maintenance dose of 200mg over 8 days. Recent pharmacokinetic modelling suggests that a loading dose of 400mg twice a day for the first day, followed by 200mg twice daily over 5 days should be sufficient to allow the attainment and maintenance of active therapeutic concentrations for SARS-CoV-2 (37). In our trial, we have chosen to use the dose also retained for the DisCovEry trial (NCT04315948).

### 1.3.3 Imatinib

Imatinib, an Abelson kinase inhibitor (Abl), targets the Abelson tyrosine-protein kinase 2 and has shown *in vitro* effectiveness on a certain number of viruses, among which HIV (38), vaccine (39), coxsackievirus (40) and Ebola virus (41,42). Abl kinase inhibitors block fusion of coronaviruses with the host cell's membrane (43). Replication of SARS-CoV and MERS-CoV is inhibited by imatinib (44,45). This drug has been used for a long time as a chronic treatment in people suffering from chronic myeloid leukaemia, many of them are elderly, and has demonstrated an excellent tolerance (46–48). It is thus an interesting drug to be evaluated in an outpatient trial targeting people over 65 years-old.

### 1.3.4 Favipiravir

Favipiravir is an antiviral selectively inhibiting the RNA dependent RNA polymerase of the numerous viruses, including influenza, hantaviruses, flaviviruses, arenaviruses, filoviruses, bunyaviruses and enteroviruses (49,50). Its evaluation in the treatment of Ebola virus disease during the epidemic that occurred in West Africa was judged to be non-conclusive in terms of efficacy (51) yet allowed improvements to knowledge of its pharmacokinetics among patients afflicted by a severe viral infection (52). The mechanism of action of favipiravir make it a credible candidate for evaluation in the context of COVID-19. Favipiravir is currently being evaluated in the context of 7 clinical trials for COVID-19. Various brief reports containing non-published data from China and Japan have declared that the preliminary results obtained with favipiravir for COVID-19 patients have been encouraging (53). The preliminary data of a clinical trial suggesting that favipiravir would reduce the duration of viral excretion and improve radiological results in patients infected by SARS-CoV-2 has been communicated in an informal manner by a Shenzhen hospital. Favipiravir at an initial dose of 1,600mg followed by 600mg thrice daily is recommended as an alternative option for patients suffering from COVID-19, who are intolerant of lopinavir/ritonavir among Chinese recommendations (24). On the basis of knowledge of pharmacokinetics of the molecule obtained from the Ebola epidemic (52,54) and of not yet data published regarding the antiviral action of favipiravir in vitro on SARS-CoV2, a regimen using higher doses of favipiravir would have better chances of allowing the attainment of therapeutic concentrations doses among patients suffering from COVID-19. In this trial, we have chosen to use that dose already used during the Ebola epidemic, higher than the dose recommended for influenza in Japan, but already administered under close clinical monitoring in humans.

### 1.3.5 Angiotensin receptor blockers (ARB)

Finally, the ARB class exhibit promising characteristics for treating COVID-19, not because of its antiviral activity but due to its potentially beneficial effect on the progression of the disease and more particularly on its ability to prevent pulmonary damage. The cellular point of entry for SARS-CoV2 is a membrane enzyme of epithelial cells of the respiratory tract: angiotensin converting enzyme 2 (ACE2) (55). ACE2 is a homologue enzyme of the angiotensin converting enzyme (ACE), which negatively regulates the renin-angiotensin-aldosterone system by converting angiotensin 2 into angiotensin (1-17). It thus has a vasculoprotective effect (56). Animals treated with angiotensin conversion enzyme inhibitors (ACEI) or with ARB have high levels of ACE2 (57). In a mouse model of SARS-CoV infection, a lowering in ACE2 activity has been confirmed. Pulmonary lesions could thus be related to this lowering in ACE2 activity and the excess of angiotensin 2. On the other hand, improvement in the pulmonary condition has been shown in mice treated with an ARB or after injection of recombinant ACE2 (58,59). Thus, a higher level of ACE2 expression among patients under chronic treatment by ARB could protect from developing a severe pulmonary disease when infected by SARS-CoV2 (60). Losartan, telmisartan, olmesartan and other compounds of the ARB class have been widely used since the 1990s for the treatment of arterial hypertension, as well as chronic kidney disease. This class is considered as having few undesirable side effects (61). We make the hypothesis that starting a treatment with telmisartan at a low dose among patients afflicted by COVID-19 at an early stage of their illness could prevent the later deterioration of their respiratory condition, while still being well tolerated.

## 1.4 Methodological justification

This study shall evaluate the efficacy and safety of several therapeutic strategies against SARS-CoV2 among those aged over 65 not presenting any hospitalisation criterion. We shall conduct a phase III randomised, open-label, controlled superiority clinical trial, with a multi-arm multi-stage (MAMS) framework.

Adults affected by COVID-19 (positive RT-PCR test) with symptoms for fewer than 72 hours at the time of testing and without hospitalisation criterion shall be included in the study and randomised, if they meet the eligibility criteria for inclusion. After randomisation, patients shall receive one of the experimental strategies or a control over 10 days. The main judgement criterion is an evaluation of the efficacy in each treatment group, on the basis of occurrence of hospitalisation or death on Day 14.

### 1.4.1 Choice of study model

Preclinical and clinical data suggesting the effectiveness of drugs against SARS-CoV-2 are still limited. A trial launched in a context of emergency should be able to integrate those considered suitable under current knowledge, while allowing them to be discarded quickly, if they do not prove immediately promising. Drugs should be able to be included during the course of the trials if new promising evidence arise in the interim.

A multi-arm, multi-stage (MAMS) study would be more efficacious in this context than separated trials with two arms (experimental treatment vs. control). This type of trial, offering the opportunity to plan in advance to change one or several aspects of the trial, is particularly suited to the current, highly-evolving, scientific context. MAMS trials allow simultaneous comparison of a certain number of experimental treatments with a single control treatment. This type of

trial provides answers more rapidly and allows the abandonment of arms for futility over planned intermediate analyses or new scientific facts or even to add an arm over the course of the trial.

Three intermediate analyses are planned over the course of the trial, after recruiting 30, 60 and 102 participants per arm. They shall cause the halting of arms, should they prove futile or toxic. At the 3rd intermediate analysis, a preliminary efficacy analysis will allow identification of any treatment, which proves to be efficacious before the end of the trial. This treatment shall then become the standard. A halt on grounds of insufficient safety shall be possible at any point, subject to approval from the DSMB, without the need for a formal statistical criterion.

Multiple statistical tests shall be conducted on grounds of the multi-stage design and the existence of several arms. Type one alpha error shall not be adjusted on grounds of the absence of an objective to extend the indication. The objective is to identify all efficacious drugs and not to identify the best.

Overall, this type of model provides us with a concomitant optimisation of the evaluation of various therapeutic strategies, while adapting itself to the international scientific context and progressively evaluating the most promising strategy or strategies.

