| NUMBER OF CENTERS                                                   | The study takes place on an outpatient basis with follow-up at home and by telephone.                                                                                                                                                                                                                                                                                                                                                                                                                                                                                                                           |
| DURATION                                                            | 
Inclusion period: 3 months
 
Participation duration: 28 days.
                                                                                                                                                                                                                                                                                                                                                                                                                                                                                                                                       |
| ANALYSIS                                                            | 
This is a Phase III trial. Sequential analyses will be performed for the primary endpoint at D14, with the following objectives:
 
 
- Intermediate analysis #1 (30 included patients per arm): futility
 
- Intermediate analysis n°2 (60 patients included per arm): futility
 
- Intermediate analysis n°3 (102 patients included per arm): futility and early efficacy
 
- Final analysis: efficacy
 
                                                                                                                               |

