## 6.2 Sample Size

### 6.2.1 Participants not taking ACEI or ARB before inclusion

The incidence assumptions on primary endpoint are based on extrapolations from aggregated data published in other contexts thus far. The DSMB will check these assumptions and recommend a sample size revision, if needed.

We assumed that the proportion of participants reaching the primary endpoint at D14 in the control arm could be up to 25%. An experimental treatment will be deemed efficient if this proportion is reduced by at least one half. We also considered a power of 80% for all tests.

Three futility (interim) analyses will be performed successively. We defined successive arm discontinuation thresholds for the one-way first type error alpha using STATA package NStageBin for conception and sample size of MAMS trials (65,66).

Two efficacy analyses (interim n°3 and primary) will be performed successively. We will use the O'Brien & Fleming procedure to define the first type error alpha for each analysis, based on the data observed at the first futility analyses (67,68).

Sensitivity analysis at D28 will be exploratory only, without impact on sample size.

Tests of difference between arms will be one-sided. Arm discontinuation thresholds and sample size for each analysis are given here below:

| Analysis    | Trigger
Number of participants in the control arm having reached D14 | Objectives     | Alpha           |
|-------------|-------------------------------------------------------------------------|----------------|-----------------|
| Interim n°1 | 30                                                                      | Futility       | 0,65            |
| Interim n°2 | 60                                                                      | Futility       | 0,45            |
| Interim n°3 | 102                                                                     | Futility       | 0,25            |
|             |                                                                         | Early efficacy | O'Brien-Fleming |
| Primary     | 169                                                                     | Efficacy       | O'Brien-Fleming |
| Sensitivity | End of trial                                                            | Efficacy       | 0,05            |

The sample size required is 169 participants by arm (845 overall). Since the "Missing as failure" procedure is used, there is no need to increase sample size to account for missing data.

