This size may vary depending on the discontinuation or addition of arms during trial:

- If one arm is discontinued: from -67 participants (discontinuation at interim analysis n°3) to -139 participants (discontinuation at interim analysis n°1)
- If one arm is added: from +169 participants (addition at the time of first participant inclusion) to +338 participants (addition after the last planned inclusion).

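### The interim looks are triggered by participants recruited in the Summary and section 1.4.1 but by control participants at Day 14 in section 6.2.1; only complete Day 14 data support the stated 80% power, and under that trigger the quoted savings per dropped arm are too large

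*Protocol*

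**What the plan says.** **Trigger by recruitment.** Section 1.4.1: "Three intermediate analyses are planned over the course of the trial, after recruiting 30, 60 and 102 participants per arm". The Summary (Analysis row) has "Intermediate analysis #1 (30 included patients per arm): futility", and likewise 60 and 102 for the second and third looks. The same row says "Sequential analyses will be performed for the primary endpoint at D14".

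**Trigger by completed follow-up.** In the section 6.2.1 table the trigger column is headed "Number of participants in the control arm having reached D14", with 30, 60, 102 and 169. The futility thresholds beside the first three are one-sided 0.65, 0.45 and 0.25.

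**Missing data.** Section 6.1 makes every primary-endpoint analysis intention-to-treat with missing values counted as failures, and section 6.3.4 counts the interim looks as part of the primary analysis. Neither section mentions participants whose Day 14 has not yet come.

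**Savings.** Section 6.2.1 says that dropping one arm changes the total "from -67 participants (discontinuation at interim analysis n°3) to -139 participants (discontinuation at interim analysis n°1"). No section mentions a recruitment pause at a look.

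**The concern.** The endpoint takes 14 days to observe and inclusion is planned over 3 months, so the two triggers are far apart in information. A look at 30 recruited per arm and a look at 30 control participants past Day 14 use different data, yet the same thresholds are attached to both. If the recruitment wording were followed at once, arms would be judged on much less information than the thresholds were set for. An effective drug could then be dropped for futility more often than designed, and that decision is hard to reverse.

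The savings figures raise a second question. They look like plain differences between 169 and the trigger counts, as if nobody were randomised during the 14-day wait. Section 6.2.3 expects one or more arms to be dropped, so these figures matter for planning.

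**Working it through.** **1. Inputs**
- Section 6.2.1: control rate up to 25%; "An experimental treatment will be deemed efficient if this proportion is reduced by at least one half", so 12.5%; "We also considered a power of 80% for all tests"; one-sided tests; looks at n = 30, 60, 102; final n = 169 per arm.
- Summary: inclusion period of 3 months.
- Assumed: uniform accrual. Total efficacy alpha is not stated for the O'Brien-Fleming tests, so final one-sided 0.025 and 0.05 are both shown. Lowering 0.025 to 0.0238 moved power by at most about half a point in the scenarios checked.

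**2. Reproducing the plan's design with complete Day 14 data**

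Stage power = Φ[(0.125 − z·SE0)/SE1], with SE0 = √(2 × 0.1875 × 0.8125/n) and SE1 = √((0.25 × 0.75 + 0.125 × 0.875)/n).

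| n per arm | z | SE0 | SE1 | Stage power |
|---|---|---|---|---|
| 30 | −0.385 | 0.1008 | 0.0995 | 95.0% |
| 60 | 0.126 | 0.0713 | 0.0703 | 95.1% |
| 102 | 0.674 | 0.0547 | 0.0539 | 94.9% |
| 169 (alpha 0.025) | 1.960 | 0.0425 | 0.0419 | 84.1% |

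Overall power is the joint probability of passing all four, with correlation √(n_i/n_j) between looks i < j. At final alpha 0.025 it is 79.5% with pooled variance, 80.0% unpooled and about 80.5% by binomial simulation. The stated 80% and N = 169 therefore reproduce. At final alpha 0.05 the result is 84.5% to 85.4%.

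**3. Outcomes available at an immediate recruited-count look**

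Accrual is 169/91 = 1.86 per arm per day, and 1.86 × 14 = 26 per arm are still inside their 14 days. Completers per arm are 30 − 26 = 4, 60 − 26 = 34 and 102 − 26 = 76.

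Scoring the pending 26 as failures at look 1 gives expected proportions of (26 + 4 × 0.25)/30 = 0.900 and (26 + 4 × 0.125)/30 = 0.883. The expected difference shrinks from 0.125 to 0.017. The chance that a drug halving the risk passes look 1 falls from 95% to about 83%.

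**4. Overall power with an immediate look (simulation, 25% against 12.5%; final alpha 0.025 / 0.05)**

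| Handling of pending participants | 3-month accrual | 6-month accrual |
|---|---|---|
| Counted as failures | 63% / 66% | 76% / 80% |
| Completers only | 65% / 69% | 73% / 77% |
| Events to date (event times uniform over 14 days, assumed) | 73% / 77% | 78% / 82% |
| Followed to Day 14 before the look | 80% / 85% | 80% / 85% |

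**5. Savings under the Day 14 trigger, no pause**

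The stated figures are 169 − 102 = 67 and 169 − 30 = 139. Allowing for those randomised during the wait, the saving is 169 − n − (14 × daily accrual). The last term is 26 at 3 months and 14 × 169/180 = 13 at 6 months.

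| Look | Stated | 3-month accrual | 6-month accrual |
|---|---|---|---|
| 1 (n = 30) | 139 | 113 | 126 |
| 2 (n = 60) | not given | 83 | 96 |
| 3 (n = 102) | 67 | 41 | 54 |

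Time for data cleaning and board review would reduce these further.

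**The case against.** The best defence is that the recruitment wording is shorthand. The Summary ties the looks to the Day 14 endpoint, section 6.1 labels each look as being at D14, and section 6.2.1 is the statistical section with an explicit trigger column. On that view the first 30, 60 and 102 included are followed to Day 14 and then analysed, and no power is lost. This is a reasonable reading and the likely intent. But the Summary and section 1.4.1 do not state it, and nothing says which section prevails. It also does not rescue the savings: waiting for Day 14 while recruitment continues is what makes 67 and 139 too large.

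A second defence is that an outcome not yet due is not a missing value, so the missing-as-failure rule was never meant for pending participants. That is fair, and the protocol does not say the rule covers them. It does not exempt them either, and it applies the rule to every primary-endpoint analysis. Using completers only would avoid the rule but still gives 65% to 69% at 3-month accrual.

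Third, the savings figure is a planning remark on which no test, threshold or maximum sample size depends. That is correct, and it limits the weight of that part.

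A reader might infer that the protocol as written cuts power from 85% to 66%. The documents do not support this. The stated power is 80%. The 85% needs a final one-sided alpha of 0.05, which the table gives only for the Day 28 sensitivity analysis. The 66% is one scenario: that alpha, an immediate look, 3-month accrual and pending participants scored as failures.

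**Conclusion.** The trigger is stated in two incompatible ways, and the design's own figures fit complete Day 14 outcomes at 30, 60 and 102. On that basis power is about 80% (final one-sided alpha 0.025, assumed) or 85% (0.05).

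The consequences are conditional:
- **Look taken at once on the recruited count:** power is about 63% to 82% across both alphas, 3- to 6-month accrual and three ways of handling pending participants. At 3 months with pending participants as failures it is 63% or 66%.
- **Look taken at Day 14 without a pause:** power is as designed, but the saving per dropped arm is about 41 to 113 at 3-month accrual (54 to 126 at 6 months), against the stated 67 to 139.

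It would be tempting to add the two harms together. They arise under different readings: with an immediate recruited-count look, 67 and 139 are arithmetically right; with the Day 14 trigger, there is no power loss. What does hold is that, without a recruitment pause, no single reading gives both the designed power and the stated savings.

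**What to change.** 1. In the Summary and section 1.4.1, use the section 6.2.1 trigger: 30, 60 and 102 control participants having reached Day 14.
2. In section 6.1, state that at interim looks missing-as-failure applies only to participants whose Day 14 date has passed. Those not yet at Day 14 are left out of that look, whether or not they have already had an event, so that numerator and denominator describe the same people; they enter at a later analysis.
3. In section 6.2.1, restate the saving per dropped arm as about −41 to −113, with the uniform 3-month accrual assumption beside it. Alternatively, state that recruitment pauses at each look and keep −67 to −139.

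The cost is wording and one restated figure. Each look comes about 14 days later than an immediate recruited-count look would, and the saving shown is less favourable. Sample size and thresholds do not change.
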